#### Qualitative analyses

All focus groups and interviews will be transcribed verbatim. Thematic analysis (TA)^62^ and the theoretical framework of acceptability^63^ will be used, allowing for both inductive and deductive coding. Members from the PPIE group will provide feedback on emerging analyses.

#### Economic analyses

We will evaluate the feasibility of conducting an economic evaluation of CR, by exploring the costs and outcomes associated with CR compared with standard care. We will codesign a health-resource use questionnaire with our PPIE group to capture any changes in healthcare resource use during the study, which will be completed by CYP and their guardians. We will explore resource use from the perspective of the NHS and personal social services, as well as taking a wider perspective to examine if there are any patient out-of-pocket expenses. We will also examine the resources and their associated costs required to develop and deliver the intervention.

We will measure health outcomes using two measures, as described above: the CHU-9D and PedsQol.^64^ The CHU-9D has a published value set in which to generate utility scores,^56^ and therefore, quality-adjusted life-years. There is also a published mapping algorithm to transform the PedsQol to the EQ-5D.^64 65^ We will examine the acceptability of both measures to the CYP and assess data completeness, to inform which questionnaire is most appropriate for use in the definitive study, or if indeed, another measure of PedsQol would be more appropriate.

We will conduct a preliminary economic evaluation using the data collected, to determine whether CR plus TAU would be cost-effective from the perspective of the NHS and Personal Social Services.

Multiple imputation and censored data analysis techniques will be used to separately impute missing observations from participants who complete follow-up, and missing follow-up data for participants lost to follow-up. The primary and sensitivity economic analyses will be controlled for key baseline covariates or characteristics. Cost-effectiveness acceptability curves will assess the likely cost-effectiveness of the intervention and uncertainty in the observed data. This cost-effectiveness analysis will be limited due to the sample size and the overall health economic work will focus on informing a definitive trial.

### Trial management and oversight arrangement

The trial is managed by a TEC, which includes those individuals responsible for the day-to-day management of the study including the chief investigator, coinvestigators and identified collaborators, principal investigators (PIs) and the study statistician. Notwithstanding, the legal obligations of the sponsor and chief investigator, the TEC has operational responsibility for the conduct of the study including monitoring overall progress to ensure the protocol is adhered to and to take appropriate action to safeguard the patients and the quality of the study. There will also be PPI groups (adult and CYP), which will meet at least quarterly and provide advice and feedback on a range of trial-related activities, for example, reviewing study documents. The end of the study will be reported to the REC within the required time frame if the study is terminated prematurely. Investigators will inform patients of any premature termination of the study and ensure that the appropriate follow-up is arranged for all involved. Following the end of the study, a summary report of the study will be provided to the REC within the required timeframe.

### Data management

Participants will be allocated a study identity code number for use on all study documents and the electronic database. The study team will make a separate confidential database for the participant’s name, date of birth and study identity code to permit identification of participants enrolled in the study, for example, for follow-up. All other information will be anonymised. All study documents (including participant’s written consent forms) which are to be held at the participating centres will be held in strictest confidence. Access to patient information shall be restricted to authorised persons. Data will only be available through restricted, shared areas on the secure Greater Manchester Mental Health (GMMH) and University of Manchester computer systems (password and username secured). Baseline and follow-up data, which is anonymous data, will be stored in locked filing cabinets at GMMH. These data will be entered into an electronic database for analysis purposes by study team members blind to trial arm allocation. All computers are password protected and adhere to the secure storage policies of the NHS trust and University of Manchester.

### Safety reporting

Adverse events (AEs) and serious AEs (SAEs) will be monitored throughout the study. AEs are defined as any untoward medical occurrence in a patient or study-specific intervention and which does not necessarily have a causal relationship with the intervention (ie, deterioration in cardiac health not associated with the intervention). SAEs are defined as AEs that result in death, are life-threatening or require hospitalisation. Adverse reactions (ARs) are an untoward medical or unintendical medical response in a patient to a study specific intervention which has a causal relationship with the intervention (ie, physical injury due to the intervention). Serious ARs (SARs) are defined as ARs that result in death, are life-threatening or require hospitalisation. All AEs, SAEs, ARs and SARs will be reviewed by the trial’s child clinical psychologist and paediatric consultant cardiologist within 24 hours of reporting. Any AEs identified as likely to be caused by the intervention during the period of recruitment or intervention on the study will be recorded at the study site using an AE/SAE record form which will be completed by the health professionals. Study RA and study PIs will be informed, and information inputted onto a secure database. The CIs will also assess if the nature of the event is likely to have been induced because of the study intervention or processes. Any that are deemed be serious and related to the intervention will be reported to the sponsor, the study executive committee and ethics committee within 24 hours of the event.

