### Criteria for discontinuation

Participants may withdraw from the study at any time, without any consequences to themselves, their healthcare or their ability to take part in future research. Participants who withdraw will continue to receive usual care. Participants can also be withdrawn at the request of the chief investigator or cardiology service, but this would only happen if a participant’s life or long-term health or welfare was at risk from continued participation in the study.

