### Ethics and dissemination

The study received full ethical approval on 14 February 2023, from North West—Greater Manchester East Research Ethics Committee, Research Ethics Committee (REC) REC ref: 22/NW/0367, IRAS ID 319134. The trial has been registered with ClinicaTials.gov (NCT05968521) and with ISRCTN (ISRCTN50031147). The study protocol used was Version 6: 21 June 2023. Any modifications to the trial will be submitted for further ethical approval and approved changes will be documented and communicated to the REC, trial registry, executive committee and all relevant parties. The study will be conducted in accordance with the ethical principles that have their origin in the Declaration of Helsinki (1996), the principles of Good Clinical Practice and the UK Policy Framework for Health and Social Care Research (2017). GMMH acts as the sponsor for this study. As the sponsor is an NHS organisation, the NHS indemnity scheme will apply. Participating sites will be liable for clinical negligence and other negligent harm to participants taking part in the study and covered by the duty of care owed to them by the sites concerned.

Written informed consent will be obtained from all participants and their parents/caregivers. Participants will be free to withdraw from the study at any time without providing a reason or their care being impacted. All the information collected during this trial will be confidential and held in accordance with NHS Data Protection guidelines and Good Clinical Practice guidelines. Confidentiality will only be breached if participants disclose information, which may indicate that there is a risk of harm to themselves or others. Every opportunity to discuss any possible breaches of confidentiality with participants will be taken prior to informing any appropriate agencies, for example, children and adolescent mental health services, general practitioner (GP) or accident and emergency (A&E) services.

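### The three-criterion definition of seriousness keeps a related event with lasting harm, but no threat to life and no admission, out of the 24-hour report to sponsor, executive committee and ethics committee

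*Protocol article*

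**What the plan says.** All of the following is in the protocol article.

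- **Safety reporting, serious adverse events (SAEs).** "SAEs are defined as AEs that result in death, are life-threatening or require hospitalisation".
- **Safety reporting, serious adverse reactions (SARs).** The same list is repeated for events with a causal link to the intervention: "Serious ARs (SARs) are defined as ARs that result in death, are life-threatening or require hospitalisation".
- **Safety reporting, expedited report.** "Any that are deemed be serious and related to the intervention will be reported to the sponsor, the study executive committee and ethics committee", with a limit of 24 hours from the event.
- **Safety reporting, review of every event.** "All AEs, SAEs, ARs and SARs will be reviewed by the trial’s child clinical psychologist and paediatric consultant cardiologist within 24 hours of reporting". Adverse events thought likely to be due to the intervention are also recorded on a site form whatever their seriousness, the research assistant and principal investigators are told, and the chief investigators consider causality.
- **Criteria for discontinuation.** "Participants can also be withdrawn at the request of the chief investigator or cardiology service", with the limit that "this would only happen if a participant’s life or long-term health or welfare was at risk from continued participation in the study".
- **Trial management and oversight arrangement.** The chief investigator and the principal investigators are members of the trial executive committee. The ethics committee receives a summary report after the study ends.

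**The concern.** Both definitions are closed lists. Neither has a criterion for lasting harm or loss of function, and neither leaves room for a clinician to judge an event important on other grounds. Because seriousness is one of the two conditions for the expedited report, a gap in the definition is also a gap in what the sponsor and the ethics committee are told while the trial is running.

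The gap lies where this intervention could plausibly do harm. Eligible children include those with arrhythmia, cardiomyopathy and heart failure, and they are offered group exercise with a psychological component. The article's own example of an adverse reaction is physical injury caused by the intervention. Such an injury could leave a permanent deficit and be treated entirely as an outpatient.

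The article elsewhere recognises harm of this kind as grave: a threat to long-term health or welfare, short of a threat to life, is among the grounds for withdrawing a child. The seriousness criteria contain nothing that corresponds to it.

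**Working it through.** The article gives no figure to reproduce, and the point depends on no rate, effect size or sample size. The check sets the sections side by side and follows one event through them.

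**Criteria compared**

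| Ground | SAE and SAR definitions (Safety reporting) | Withdrawal by chief investigator or service (Criteria for discontinuation) |
|---|---|---|
| Death | yes | not applicable |
| Threat to life | yes | yes |
| Admission to hospital | yes | not named |
| Long-term health | no | yes |
| Welfare | no | yes |

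**One event traced.** Take a child who suffers a permanent injury in a CardioActive exercise session, is treated without admission, and is never in danger of death.

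1. *Is it an adverse reaction?* Yes. It is untoward and caused by the intervention.
2. *Is it serious?* It is not fatal, not life-threatening and did not require admission. None of the three criteria is met, so it is non-serious.
3. *Does it trigger the 24-hour report?* The rule needs serious and related. The event is related but not serious, so the rule does not apply.
4. *Could it meet the withdrawal ground?* Yes, if continuing would put long-term health or welfare at risk.
5. *What still happens?* The psychologist and cardiologist review it within 24 hours of reporting. As a likely intervention-related event it is recorded, the principal investigators are informed, and the chief investigators assess causality. Through their membership, individual members of the executive committee know of it.
6. *What does not happen?* The article describes no step that sends this individual event to the sponsor or the ethics committee. The end-of-study summary is the only later report to the ethics committee that it mentions, and nothing says that the summary lists individual non-serious events.

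**Scale.** The article gives no event rate. The only bound available is exposure: 50 children in the CardioActive arm, each offered six sessions, gives at most 50 × 6 = 300 child-sessions. How many would produce an event of this type cannot be derived from the document.

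**The case against.** The strongest reply is that the safety system does not rest on seriousness alone. Every reported event, serious or not, is seen by two clinical roles within 24 hours, and events likely to be related reach the principal investigators, who sit on the executive committee together with the chief investigator. That stands. A reader might infer that a non-serious event of this kind would never be escalated; the text does not support that. What is lost is the mandatory report to the sponsor, the committee as a body and the ethics committee.

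The second reply is that the withdrawal rule and the seriousness definition do different jobs. One looks forward to the risk of continuing; the other classifies an event by its outcome. A child may be withdrawn on welfare grounds with no adverse event at all. That stands too. The discontinuation threshold is wider than the seriousness definition, but it does not contradict it.

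Other stronger readings also fail:

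- *That every related event treated without admission is missed, however severe.* Life-threatening is a separate criterion that needs no admission, so a life-threatening arrhythmia treated and discharged the same day is serious.
- *That planned admissions would become SAEs and blur a comparison between arms.* An adverse event must first be untoward, which a scheduled procedure is not. The Quantitative analyses section plans no hypothesis testing, and no between-arm safety comparison is described.
- *That the definition breaches the commitment to* "the principles of Good Clinical Practice". The article does not set out what those principles require on seriousness, so the point cannot rest on them.

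Finally, the full protocol (Version 6) is not shown and may hold a longer definition. That lowers confidence, but the article words its three criteria as the definition, twice, rather than leaving the matter to the fuller document.

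**Conclusion.** The point holds in a narrow form. If the article's rule is followed as written, a related event that causes lasting harm or loss of function, without threat to life and without admission, is non-serious and falls outside the 24-hour report. The article gives no other route for that individual event to the sponsor or the ethics committee, although it counts a risk to "life or long-term health or welfare was at risk from continued participation in the study" as grave enough to remove a child.

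The conclusion assumes that the three criteria are applied literally and that Version 6 does not widen them. It also depends on the event being related, since relatedness is the second condition for the report. The overlap between a withdrawal on these grounds and a non-serious event is possible, not automatic. The size cannot be stated because no event rate is given. In a trial with 50 children in the intervention arm few such events are likely, but each would be one that those bodies should hear about promptly. No efficacy or feasibility estimate is affected.

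**What to change.** Reconcile Safety reporting with Criteria for discontinuation:

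1. Add two criteria to both the SAE and the SAR definition: persistent or significant disability or incapacity, and any event judged medically important by the child clinical psychologist or paediatric consultant cardiologist who already review every event.
2. Require a documented seriousness assessment of any adverse event that leads to a withdrawal requested by the chief investigator or cardiology service. The event should not become serious automatically, because seriousness would then follow from a management decision and not from the event itself.
3. If Version 6 already has the wider definition, a short correction to the article is enough.

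The grounds for withdrawal need not change. The cost is revised definition wording, an edit to the AE/SAE form, submission of the modification for ethical approval if the protocol itself has to change, and probably a few more expedited reports. The reviewers are already in place, so no new role is needed.

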### Data collection

The planned study recruitment date is March 2024, with the end of follow-up marking study completion in June 2025. There will be three follow-up assessment points: baseline, 12 weeks (end of treatment) and 24 weeks (follow-up). To ensure completeness of the questionnaires, participants will be asked to arrange a visit, either at an NHS site or in their own home, at each time point. Participants’ total time involvement in the study will be 24 weeks. Participants will be reimbursed with a £10 shopping voucher for completing each assessment.

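### Adverse events are monitored and reviewed whatever their cause, but the one recording rule covers those judged likely caused by the intervention, in an undefined window, so recorded harms could not be compared by arm

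*Protocol article*

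**What the plan says.** The Safety reporting section of the protocol article makes six statements that bear on this point, in this order:

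- **Scope.** "Adverse events (AEs) and serious AEs (SAEs) will be monitored throughout the study".
- **Definition.** An adverse event is one that "does not necessarily have a causal relationship with the intervention". The example given is a worsening of cardiac health unrelated to the programme. Events with a causal link have their own category, adverse reactions.
- **Review.** "All AEs, SAEs, ARs and SARs will be reviewed by the trial’s child clinical psychologist and paediatric consultant cardiologist within 24 hours of reporting".
- **Recording.** "Any AEs identified as likely to be caused by the intervention during the period of recruitment or intervention on the study will be recorded". This is done at the site on an AE/SAE form. A research assistant and the site investigators are then informed, and the information goes into a database.
- **Second look at causality.** "The CIs will also assess if the nature of the event is likely to have been induced because of the study intervention or processes".
- **Escalation.** Events found to be serious and related "will be reported to the sponsor, the study executive committee and ethics committee within 24 hours of the event".

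Four other sections matter. Treatment as usual describes routine outpatient care with no study intervention. Data collection sets assessments at baseline, at 12 weeks (when treatment ends) and at 24 weeks. Recruitment and allocation places baseline data collection before randomisation. Outcomes has all measures, including the two walk tests, taken at every assessment.

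**The concern.** Scope, definition and review cover every event in either arm. The recording sentence filters events by cause and by time, and it is the only sentence that governs what reaches the form and the database. What it keeps is in effect the adverse-reaction category, so the broad definition of an adverse event has no consequence for the data. The section's own example of an adverse event would not have to be recorded.

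The programme is group exercise for 11 to 16 year olds with heart conditions, including cardiomyopathy, arrhythmia and heart failure, and the study is meant to inform a definitive trial. Events are to be expected in this population without any programme, and a usual-care count is what shows that background. If one arm cannot produce records, the counts say nothing about it, even descriptively. An event judged unrelated at first and left unrecorded also leaves no form to return to if the judgement later looks wrong.

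**Working it through.** The article states no safety figure, so there is none to reproduce. The check is mainly textual.

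**1. Cause.** The definition includes events without a causal link, and the review covers all categories. The recording sentence requires a likely causal link to the intervention. An unrelated event is therefore monitored and reviewed, but no sentence requires it to be recorded. This holds for serious events too, because they are defined as a subset of adverse events.

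**2. Arm.** Usual care contains no study intervention, so an event there can hardly be identified as likely caused by it. The later assessment by the chief investigators is wider, since it also covers study processes. A walk-test injury in a usual-care participant would fall under that assessment but not under the recording rule.

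**3. Time.** Monitoring runs throughout the study. The recording window is tied to recruitment or intervention. Treatment ends at 12 weeks and follow-up at 24, and the window does not name those last 12 weeks. The recruitment period is not defined. If it means calendar time, it could overlap follow-up for participants who enter early.

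**4. Order.** The causality filter comes before the form. The chief investigators' own assessment is described after form and database entry, so an event screened out at the first step need not have a record when the second is made.

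**5. Illustrative size.** Inputs: 50 per arm and 100 in total (Sample size calculation); 12 and 24 weeks (Data collection). Assumption: complete follow-up.

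- All planned observation: 100 x 24 = 2,400 participant-weeks.
- Usual care: 50 x 24 = 1,200, of which essentially none can yield a record, because of the causality filter.
- CardioActive, if the window is the 12-week intervention period: 50 x 12 = 600, and 600 / 2,400 = 25%.
- CardioActive, at the extreme where the undefined window covers all follow-up: 50 x 24 = 1,200, and 1,200 / 2,400 = 50%.

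The share thus depends on how the window is read. The absence of usual-care records does not.

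**6. The two 24-hour deadlines (minor).** Suppose an event is reported t hours after it occurs and review takes r hours, with r at most 24. Classification is complete at t + r hours, while notification is due at 24 hours from the event. With immediate reporting (t = 0) the two always fit. With any delay, t + r can exceed 24, and with t above 24 the notification deadline has passed before the report arrives.

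**The case against.** **A reader might infer that usual-care and follow-up events are never captured.** The documents do not support that. Monitoring runs throughout the study without limit by arm, and the review of all events presupposes that unrelated ones are reported. The recording sentence does not contain the word only. The service-use questionnaire asks about health and social care at each visit without restriction by arm, and reasons for drop-out are recorded where possible. What stands is narrower: no sentence requires such events to be entered as adverse events, and a service-use count recalled by parents is not adverse event recording.

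**The 25% might be read as a result.** It is one reading of an undefined window, as step 5 of the working shows.

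**It might also be inferred that causality is judged by people who know the allocation.** The article does not say who makes the first judgement or whether they are blinded. It lists the quantitative research assistants and the statistician as blinded, which makes the inference plausible but does not document it.

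**Comparing harms is not a stated objective.** The primary outcomes are feasibility and acceptability, and no hypotheses are tested. With 50 per arm, zero events would still leave a 95% upper bound of 1 - 0.05^(1/50) = 5.8% (one-sided) or 1 - 0.025^(1/50) = 7.1% (two-sided). This stands, and it limits the loss to descriptive safety data. It does not excuse a rule that empties one arm of records.

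**The article condenses a full protocol (version 6) that is not shown and may settle the matter.** That is possible. But the article states a rule here, so this is not a detail left out. If the full protocol differs, the published sentence is wrong and still needs correcting.

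**Conclusion.** The concern holds as an internal contradiction with a practical consequence. Events are monitored and reviewed whatever their cause, while the one recording rule is filtered by cause and by an undefined window. Followed literally, it gives essentially no adverse event records from usual care, does not require CardioActive events first judged unrelated to be recorded, and leaves weeks 12 to 24 unnamed.

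The size is the loss of a descriptive comparison by arm and of the chance to revisit causality. It is not a failed test, because none is planned. The conclusion about usual care rests only on that arm receiving no intervention. The 600 of 2,400 participant-weeks is illustrative and assumes a 12-week window and full follow-up. The mismatch between the two 24-hour deadlines is a minor drafting point that bites only when reporting is delayed.

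**What to change.** Replace the recording sentence so that:

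- all adverse events and serious adverse events in both arms are recorded on the AE/SAE form, whatever their presumed cause;
- recording runs from consent to the 24-week visit. Starting at randomisation would miss events in the baseline walk tests, which come before it;
- the same prompt is used in both arms at the 12- and 24-week visits;
- relatedness, to the intervention or to study processes, is assessed afterwards and stored as a separate field;
- events are reported descriptively by arm.

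In the same amendment, reconcile the two 24-hour deadlines, one of which runs from reporting and the other from the event.

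The cost is one rewritten paragraph, a short prompt at visits already planned and somewhat more data entry. The change concerns what is recorded, not how participants are cared for.

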**Trial registration number:**

ISRCTN50031147; NCT05968521.

STRENGTHS AND LIMITATIONS OF THIS STUDYThe study will evaluate anovel cardiac rehabilitation intervention (CardioActive) for children and young people with heart conditions, which includes both mental and physical health support based on evidenced-based psychological theory.As the study is feasibility, the sample size is limited and the study is not powered to determine efficacy.Data collection will be conducted by researchers blind to participant allocation

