### Recruitment and allocation

Participants will be screened for eligibility during routine clinic appointments by clinicians and/or cardiac team members. Clinicians/cardiac team members will ask eligible patients and their parent/caregiver if they are interested in hearing more about the research study and if their contact details can be passed onto the research team. The research team will then contact eligible and interested patients and their caregivers to provide further information about the study, answer any questions, arrange for consent to be obtained and collect baseline data. Once baseline data have been collected, participants will be randomised to a study arm using sealed-envelope software.^48^ Randomisation (at the individual level) will be independent and concealed, after stratification by age (11–13 and 14–16) and sex (male and female). Within strata, allocation will occur within blocks of size 4 or 6, determined at random and with equal probability by the software. This will minimise future allocation ‘predictability’. A member of the research team not blinded to allocation will contact parents/caregivers to inform them of the allocation within 2 days. Blinding of allocation will be maintained for quantitative research assistants (RAs), and the trial statistician until all outcome measures for all subjects have been collected. The trial executive committee (TEC) will regularly monitor any unblinding’s and corrective action will be implemented if needed.

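### The safety-reporting route does not exclude the blinded research assistants or the statistician, so a report of an intervention-related event can unblind individual CardioActive participants

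*Protocol article*

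**What the plan says.** Three sections of the protocol article bear on this.

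- **Who stays blind.** Under Recruitment and allocation: "Blinding of allocation will be maintained for quantitative research assistants (RAs), and the trial statistician until all outcome measures for all subjects have been collected". That same section describes someone who is not blind: "A member of the research team not blinded to allocation will contact parents/caregivers to inform them of the allocation within 2 days". It also gives the TEC the task of monitoring unblindings.
- **Where blinding is relied on.** The strengths and limitations box states: "Data collection will be conducted by researchers blind to participant allocation". Data management says of the baseline and follow-up data: "These data will be entered into an electronic database for analysis purposes by study team members blind to trial arm allocation".
- **Who hears of related events.** Safety reporting has adverse events judged probably due to the intervention recorded on a form at the site. It continues: "Study RA and study PIs will be informed, and information inputted onto a secure database". Those that are both serious and related "will be reported to the sponsor, the study executive committee and ethics committee"; the time limit is 24 hours.
- **Who sits on the committee.** Trial management and oversight arrangement lists the TEC members, among them "coinvestigators and identified collaborators, principal investigators (PIs) and the study statistician".

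**The concern.** The notice to the RA is not general safety information. It concerns events already thought to result from the intervention, and only one arm receives the intervention. Telling a blinded assessor that a particular child has had such an event amounts to telling the assessor that child's arm. The same holds for a statistician who sees a participant-level report of a serious related event, or who takes part in the committee's review of unblindings.

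The exposure is one-sided, because this route cannot produce a related event in the usual-care arm. Any resulting assessor bias would therefore differ between arms. The outcomes most open to it are the 6-minute walk test, which depends on effort, and the Incremental Shuttle Walk Test, where one of the stopping rules turns on whether the child can keep up the required speed. These are secondary outcomes. A procedure tried out in a feasibility study is likely to be carried into the definitive trial, so the gap is worth closing now.

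**Working it through.** The plan gives no figure on this point, so there is nothing to reproduce. The check sets the sections side by side.

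1. **Does a related-event notice reveal the arm?** The Abstract compares CA plus usual care with usual care alone, 50 children per arm. An event attributed to the intervention can belong only to a child allocated to CA. If the child is identifiable, the notice points to the arm.

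2. **Is the RA who is informed a blinded one?** Recruitment and allocation blinds the quantitative RAs, and that is where the abbreviation is introduced. The article describes no other RA. Safety reporting says only Study RA, without stating whether that person is blinded. The text therefore permits notice to a blinded assessor but does not require it.

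3. **Does the committee that is informed include the statistician?** Safety reporting names the study executive committee, and the membership list is that of the TEC. Ethics and dissemination uses both names for the body that controls publication, which suggests one committee. Quantitative analyses refers to a single statistician, so the study statistician and the trial statistician are probably the same person. On that reading, serious related events reach someone who is meant to stay blind. No section says that the statistician is excused.

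4. **Does a study code protect against this?** Data management puts a code number on all study documents. An RA who completes assessments under those codes, or a statistician who holds data indexed by them, could still link a coded report to a participant.

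5. **Is the timing harmful?** The form covers events during recruitment or intervention. Data collection places the end of treatment at 12 weeks, with assessments at 12 and 24 weeks. A notice from the treatment period will usually come before one or both follow-up visits.

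6. **How many children?** The article gives no rate of related events. As an illustration only, assume that k of the 50 CA children have one, with k from 0 to 5.
   - Share of the CA arm = k/50. For k = 0, 1 and 5 this is 0%, 2% and 10%.
   - Follow-up visits after a notice are at most 2 × k, out of 50 × 2 = 100 planned in the CA arm. For k = 0, 1 and 5 this is at most 0, 2 and 10 visits.
   - Usual-care arm: 0 of 50 by this route.

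   The visit counts are upper limits. They require that the RA informed is a blinded assessor, that this RA assesses that child, and that the event precedes both visits.

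**The case against.** The strongest reply is that no contradiction is proven for the RA. Only the quantitative RAs are blinded, the article has an unblinded team member and a nested qualitative study, and the Study RA may be someone outside the blinded group. This stands. A reader might infer that the safety route necessarily breaks the assessors' blinding, and the documents do not support that. They show that the text fails to exclude a blinded RA.

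A reader might also infer that all intervention-related events reach the statistician, or that the statistician could learn the allocation list. Neither is supported. The committee receives only events that are both serious and related, and each report exposes only the participant concerned. Knowing the arm of a few children also gives no evident way to shape a mainly descriptive analysis plan.

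Other replies stand in part:

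- The first notice is a provisional judgement. The chief investigators then consider whether the intervention or the study processes induced the event, and processes such as the walk tests occur in both arms. A notice is therefore strong evidence of allocation rather than certain proof.
- The TEC monitors unblindings with corrective action, and access to patient information is restricted. Corrective action comes after the event, however, and the body that does the monitoring seats the statistician.
- An article may leave masking of safety reports and database permissions to the full protocol. That would answer a complaint about missing detail. Here the article itself states who is told, who sits on the committee and who must stay blind, and these statements do not fit together as written.
- The consequences are limited. The primary outcomes are feasibility and acceptability, and the co-primary symptom measures are completed by children, with caregivers also completing the Strength and Difficulties Questionnaire. The shuttle test is paced by an audio signal and has listed stopping criteria. No test of effectiveness is planned.

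**Conclusion.** The point holds in a limited form. Recruitment and allocation, Trial management and oversight arrangement, and Safety reporting must be reconciled, because following them as written can disclose the allocation of individual CA participants to people who are meant to remain blind.

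For the RA this is an ambiguity: the article does not say that the person informed is unblinded. For the statistician the link is firmer, but it rests on two likely readings, namely that the executive committee is the TEC and that the study and trial statistician are one person. Both parts also assume that reports identify the participant, directly or by code.

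The number of children affected cannot be derived from the article and is probably small, smaller still for serious related events. Any assessor bias would bear mainly on the secondary walk tests and little on the primary feasibility outcomes or the questionnaires. The reason to act is that the leak is confined to one arm and the repair is nearly free.

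**What to change.** - In Safety reporting, replace Study RA with the unblinded research team member already described under Recruitment and allocation.
- State that information on whether an event is related to the intervention is kept from the quantitative RAs and the statistician until outcome collection is complete for all participants.
- State that the statistician neither receives nor discusses participant-level reports of serious related events or of unblindings, and leaves the committee for those items.

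The cost is a few sentences, the management of database access rights, and the statistician's absence from those items. No new post is needed, since the unblinded role exists. Safety reporting need not slow down, because the clinical review and the onward reports to the sponsor and the ethics committee are unchanged.
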